### Sample size

Statistical power (+/- 95% CI) to detect a fixed effect the size of 0.15 or 0.25 (left and right panels, respectively) and with a random effect of clusters (health stations), measured in standard deviations, was set to 0.1 or 0.25 (top and bottom panels, respectively). Power was calculated over a range of sample sizes using the power Curve function from the *simr* R library. The number of clusters (health stations) is six, i.e., three per treatment group. Each data point and associated confidence interval are estimated from 1000 Monte Carlo simulations. The results indicate that a total sample size of at least 300 participants (approximately 50 parents/child pairs from each center) is needed to ensure adequate power, given that the effect size is no smaller than 0.25 (Fig. 4).

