### Outcomes

#### Primary outcome measures

**Change in poor parental knowledge of children’s oral health**

The questionnaires completed by IM before and after a culturally adapted informational intervention will be used to measure the change in parental knowledge. Responses of parents to the first questionnaire, when the child is 0–6 months, and then when the child is 18–24 months were collected. The changes between and within the control and intervention groups will be evaluated.

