**Change in poor parental behavior regarding children’s oral health**

The questionnaires completed by IM before and after culturally adapted informational intervention were the basis for measuring the change in parental behavior. Similarly for this outcome, the changes between and within the control and intervention groups will be assessed.

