### Statistical analysis

The data will be analyzed using STATA and SPSS version 24 (SPSS Inc., Chicago, II, USA). Descriptive statistics such as mean and standard deviation for continuous variables and frequency and percentage for categorical variables will be presented. Univariable analysis will be based on cross tabulation and Chi Square statistics. Independent sample t test will be used to assess how sum scores of knowledge, attitudes and the parent’s own oral hygiene and dietary habits varied according to the parents’ age, educational level, and duration of residence in Norway. Differences between intervention and control groups will be analyzed using T-tests and associations will be quantified using eta coefficients. A two-sided significance level of 5% will be applied in all analyses.

Primary analysis will follow an “Intention-to-treat” approach. Comparison between the intervention and control groups at baseline and follow-up to calculate intragroup changes of outcome variables will be performed using generalized linear model (GLM) repeated measures. In the secondary analysis, ‘per-protocol’ approach will be used, where the participants would be excluded if they (1) did not participate in the intervention program, (2) did not complete the questionnaires, (3) were not eligible according to the inclusion and exclusion criteria.

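### The primary intention-to-treat model is described by intragroup change, and no between-arm contrast, baseline adjustment or health-centre term is designated as primary

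*Protocol article*

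**What the plan says.** In the protocol article, *Statistical analysis* makes the primary analysis intention-to-treat and gives the model one sentence. Its subject is "Comparison between the intervention and control groups at baseline and follow-up to calculate intragroup changes of outcome variables". The method named for this is a repeated-measures GLM, with no model term identified as the treatment effect and no covariate or centre effect mentioned.

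Earlier in the same section: "Differences between intervention and control groups will be analyzed using T-tests". The time point is not given, and again there is no adjustment and no centre. The section also states: "A two-sided significance level of 5% will be applied in all analyses".

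Under *Primary outcome measures*, the knowledge outcome ends with "The changes between and within the control and intervention groups will be evaluated". For the behaviour outcome, "the changes between and within the control and intervention groups will be assessed". Neither says which comparison decides efficacy. There are two measurements: one when the child is 0–6 months, and a second at 18–24 months.

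*Sample size* calls for "a total sample size of at least 300 participants", about 50 per centre. It was simulated with six centres and a centre random effect of SD 0.1 or 0.25. The legend of Fig. 3 gives 7 centres and 475 participants.

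**The concern.** Change within an arm is not a treatment effect. Control parents receive the centres' regular health information, all parents gain experience as the child grows, and both arms answer the questionnaire twice. Some improvement without the intervention is therefore plausible. When within-arm changes are tested at 5% beside the between-arm comparison, and nothing says which one counts, a significant change in one arm only can be taken for a difference between arms.

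A two-time repeated-measures GLM gives three tests: time, group, and group by time. Only the last is the difference between arms in change. Leaving the term open leaves the primary result open.

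The analysis also departs from the design. Centres were randomised and the sample size has a centre random effect, but the described t-tests and GLM have none.

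**Working it through.** The plan states no figure for this analysis. The 300 in *Sample size* is used only as an input. It cannot be reproduced, because the text gives no numerical power target or residual SD and Fig. 4 is not shown.

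**1. False contrast from within-arm tests.** If both arms truly change by the same amount and each within-arm test has power p, the chance that intervention is significant and control is not equals p(1−p).
- p = 0.5: 0.25
- p = 0.7: 0.21
- p = 0.8: 0.16

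At this trial's size (150 per arm, SD 1, assumed baseline–follow-up correlation r = 0.5, clustering ignored), the SE of a within-arm change is √(2(1−0.5)/150) = 0.0816.

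| Equal true change (SD) | Within-arm power | Intervention significant, control not |
|---|---|---|
| 0.10 | 0.232 | 0.178 |
| 0.15 | 0.451 | 0.248 |
| 0.20 | 0.688 | 0.215 |
| 0.25 | 0.865 | 0.117 |

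**2. Which GLM term.** In a simulation of 4,000 trials (150 per arm, effect 0.25 SD, r = 0.5, no clustering), power was 23.4% for the group main effect, 58.2% for group by time and 69.7% for the baseline-adjusted difference.

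**3. Precision at individual level.** Per-participant variance is 1 for follow-up only, 2(1−r) for change and 1−r² for baseline-adjusted. The article does not give r.

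| r (assumed) | Change | Adjusted | Adjusted / change = (1+r)/2 |
|---|---|---|---|
| 0.3 | 1.40 | 0.91 | 0.65 |
| 0.5 | 1.00 | 0.75 | 0.75 |
| 0.7 | 0.60 | 0.51 | 0.85 |

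**4. Precision with centres.** Take m = 50 per centre, residual SD 1, centre SD s, and correlation c between a centre's effects at the two times (c is not in the article). The variance per centre mean is:
- follow-up only: s² + 1/m
- change: 2(1−c)s² + 2(1−r)/m
- baseline-adjusted, slope r: s²(1 + r² − 2rc) + (1−r²)/m

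Example with s = 0.25, c = 1, r = 0.5: adjusted = 0.0625 × 0.25 + 0.015 = 0.0306. Change = 0.02. Ratio 1.53.

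| s | c | Adjusted / change at r = 0.3, 0.5, 0.7 | Adjusted / follow-up only |
|---|---|---|---|
| 0.1 | 0.5 | 0.69, 0.75, 0.82 | 0.87, 0.75, 0.60 |
| 0.1 | 1 | 0.83, 0.88, 0.93 | 0.77, 0.58, 0.37 |
| 0.25 | 0.5 | 0.75, 0.75, 0.80 | 0.82, 0.75, 0.72 |
| 0.25 | 0.8 | 1.06, 0.96, 0.90 | 0.68, 0.52, 0.40 |
| 0.25 | 1 | 1.74, 1.53, 1.32 | 0.59, 0.37, 0.19 |

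Simulation with six centres of 50 agrees closely (1.32–1.66 at s = 0.25 with stable centre effects). From the formulas, adjustment beats follow-up only whenever s²(r − 2c) < r/m, which always holds if c is at least r/2.

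**5. Leaving out the centre.** For a follow-up comparison at 50 per centre, the design effect is (s² + 1/50)/((1 + s²)/50): 1.49 at s = 0.1 and 3.88 at s = 0.25. The true size of a nominal 5% test is 2(1 − Φ(1.96/√DE)): 10.8% and 32%. A change-score comparison is affected less where centre effects are stable.

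**The case against.** The strongest reply is that the between-arm comparison is already there. The GLM sentence opens as a comparison of the two arms, t-tests between arms are planned, and both primary outcomes list between-arm change. The group-by-time term is a valid between-arm contrast under randomisation, and no passage says that efficacy will be claimed from two within-arm tests. The exact contrast and covariates may be in a statistical analysis plan that is not shown. This stands against certain stronger readings:

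- A reader might infer that within-arm change replaces the between-arm comparison. The text does not say so. It lists both and ranks neither.
- A reader might infer a fixed loss of precision: at r = 0.3–0.7, ratios of 0.65–0.85 correspond to 18–54% more participants (1/0.85 to 1/0.65). That is an individual-level result. With centre SD 0.25 and stable centre effects, change scores are the more precise choice.
- A reader might infer that change scores over-correct baseline imbalance. If the imbalance reflects stable centre differences, subtraction removes it and individual-level adjustment removes only part.
- A reader might infer significance tests between arms at baseline. The wording more naturally names the two time points of the model.

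The reply does not remove the rest. The one sentence that defines the primary analysis states intragroup change as its purpose, and the described methods omit the centre effect on which the sample size depends. These are matters the article states, not details it leaves open.

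**Conclusion.** The point holds in a limited form. A between-arm comparison is intended, but none is designated primary, within-arm changes are evaluated beside it, and neither method includes the baseline score or the health centre.

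The 16–25% false-contrast risk is conditional: it applies if efficacy is read from within-arm tests, if true change is equal in both arms, and if each test has 50–80% power. Baseline adjustment beats an unadjusted follow-up t-test in every setting tabulated (variance ratio 0.19–0.87), given centre effects at least moderately correlated over time. Against change scores it wins throughout at centre SD 0.1, but at 0.25 the direction depends on r and on how stable the centre effects are. The article gives neither. This should be corrected, and no change to the trial's conduct is needed.

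**What to change.** For each primary score, define the primary analysis as the between-arm difference at 18–24 months, with the baseline score as covariate, arm as fixed effect, health centre as random effect, a small-sample correction for 6–7 centres, and a 95% CI. State that this contrast alone decides efficacy. Report within-arm changes descriptively, without tests. Keep a change-score (group-by-time) analysis with a centre effect as a sensitivity analysis, and remove the unadjusted t-tests as tests of efficacy. Date the change before outcomes are compared by arm.

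The cost is wording and slightly more analysis work, since the baseline questionnaire is already part of the design. Intervals will be wider but honest. With six centres and 4 degrees of freedom, the multiplier is 2.78 instead of 1.96, or 2.78/1.96 = 1.42 times as wide from that source alone, before the centre variance is added.

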## Discussion

Parents of immigrant background are not able to derive much benefit from the health information currently provided at healthcare centers. This is attributed to low attendance rates, poor skills in the host language and illiteracy in terms of beliefs and behaviors which differ from those of the host population [35]. A previous Norwegian study suggests that immigrant groups in Western societies require different information packages, modified strategies, and encouragement to exercise discipline with reference to factors which have deleterious effects on general and oral health [36]. Thus, this work indicated that NW immigrant families with small children might be in great need of an early, culturally adapted intervention in the form of healthy dietary advice/guidance and early oral health care. Currently there is scarce evidence to support the efficacy of culturally tailored health interventions (interventions which take culture-specific factors into account).

### Need for intervention

Why use MI and CRFA in the present innovative intervention?

To reduce common dietary-related behavior, which contributes to the risk of obesity and dental caries in children, parents need to be educated about the sugar content of processed foods and beverages as well as the negative impact on their children’s health of frequent daily sugar consumption. Moreover, health professionals must engage in identifying children who are at risk for obesity and dental caries and provide education, screening, and referral to reduce common risk behaviors [37]. Furthermore, by engaging primary healthcare professionals, this project might contribute to solutions for different challenges, including communication when encountering parents of immigrant background seeking health and welfare services. By creating a collaborative model between primary care and dental health services, the project prioritizes services which are sustainable and cost-effective for society, resulting in user satisfaction.

This outcome has been documented in previous reports. In an Australian study, families of Iraqi, Lebanese, or Pakistani background were offered community oral health education sessions and reorienting of dental health and family services, with promising results [25]. Ninty three percent of caregivers of children aged 6–36 months reported positive behavioral changes after an intervention to improve feeding practices. The authors of this study stated that partnerships between dental and nutrition professionals offer opportunities to address key dietary behaviors that may prevent obesity and improve oral health, particularly among children at risk [11]. While intervention studies focusing on diet-related diseases in young children have reported various outcomes, MI has proved to be the most effective [38].

The main strength of this study is that it is a randomized trial, making it possible to evaluate the effectiveness of an intervention program to prevent caries and obesity. The use of cluster randomization allows the identification of the intervention effects when randomization at individual level is not appropriate. Cluster randomization may help to prevent contamination caused by sharing of information between intervention and control participants. Using a culturally adapted health intervention program, focusing on dietary- and oral hygiene practices among NW immigrant families attending primary health care centers might positively impact parental attitudes towards the oral health of their children. In this study, the collaboration between dental public health and primary health care personnel using the CRFA and MI is an innovation which offers opportunities to address key dietary behaviors that may improve general and oral health, particularly among at-risk children.

A possible limitation of this study is that data will be collected by means of a self-reported questionnaire, in which participants might be inclined to give more socially acceptable answers. The diverse backgrounds and different periods of residence in Norway might influence comparisons between groups as well as the acculturation effects. Finally, the two sessions for data collection limit the potential to draw causal inferences about the influence of parental characteristics on their hygiene/feeding practice knowledge and attitudes.

### Dissemination, sharing and utilization

We intend to disseminate the findings to the professionals most closely involved (e.g., dentists, primary care health personnel, etc.) and to extend this information to other communities in order to increase general awareness of the health care needs of immigrants and to foster interdisciplinary collaboration between oral and primary health care authorities. To improve health awareness among immigrants, educational seminars targeting newly arrived immigrants will be arranged at local health service centers, including public primary health care centers, dental public health service centers and health information days arranged by dental students. In this context the informative intervention materials produced for the present study will be of help to the primary health care medical staff to improve communication challenges with NW immigrant parents.

### Trial Status

Recruitment started in 2019,was continuing when the manuscript was submitted and is estimated to finish in 2025.

## Data Availability

The study data used will be available from the corresponding author (MM) upon request.

## List of abbreviations

BMI: Body mass index
CI: Confidence Intervals
CRFA: Common Risk Factor Approach
ECC: Early Childhood Caries
ECOHIS: Early Childhood Oral Health Impact Scale
IM: Immigrant
MI: Motivational Interviewing
N: Native Norwegian
NW: Non-western
QoL: Quality of Life
TPB: Theory of Planned Behavior
